### Randomization

Eighty random numbers will be generated by a computer and randomly divided into an intervention group and a control group with a distribution ratio of 1:1. The assigned numbers will be sealed in 80 opaque envelopes. Recruiters will enroll research subjects who meet the research conditions, agree to participate in the research, and sign an informed consent form. Subjects will randomly draw envelopes, enter their assigned groups, and have baseline measurements taken. Participant recruitment and assignment will be done by two independent researchers, blinding participants, recruiters and data collectors.

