### Setting and recruitment

Subjects will be recruited from relevant departments of three general hospitals in Anhui Province and offered gifts and free medical exams. Recruiters will present the study to breast cancer families who meet the study criteria. If patients and their families are interested in participating in this study, they will be asked to sign informed consent forms and randomly assigned. Investigators should explain to participating families that the study will not adversely affect them and that participating families can opt out of the study at any time.

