### Intervention

#### Control group

Families in the control group will receive usual care. Usual care includes the following: First, the issuance of health handbooks, which include breast cancer-related knowledge, postoperative rehabilitation exercise guidance, clinical nursing practice guidelines for preventive behavior of breast cancer-related lymphedema and a breast cancer postoperative follow-up checklist. Second, a WeChat group will be established where researchers answer questions and share disease-related knowledge with participants. Finally, Everyone will be encouraged to share positive experiences related to the disease in the WeChat group to encourage and support each other.

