Before the intervention begins, the researcher will brief the intervention group families about the program and build a relationship of trust with them. Assessors will collect baseline data, and another researcher will teach participants to use online video software. The first family meeting will be held 1 week after the patient’s surgery, and the theme will be understanding breast cancer and family resilience. The second family meeting will be held 2 weeks after surgery, and the theme will be remaining positive. The third family meeting will be held 3 weeks after surgery, and the theme will be discovering available resources. The fourth family meeting will be held 4 weeks after surgery, and the theme will be improving family cohesion. The fifth family meeting will be held 5 weeks after surgery, and the theme will be facilitating effective communication. The sixth family meetings will be held 6 weeks after surgery, and the theme will be family problems and coping. The themes of the six meetings stemmed from Walsh’s family resilience framework. The themes for the first and second meetings were from the belief systems, the themes for the third and fourth meetings were from the organizational patterns, and the themes for the fifth and sixth meetings were from the communication/problem-solving process. Formation of the main contents of the six-week intervention plan through a literature review. Then, the form and content of the intervention plan were adjusted through structured interviews with patients, family members, and medical staff in breast cancer-related departments. Finally, through two rounds of expert consultation, the content of the intervention plan was revised to ensure the scientificity and feasibility of the intervention plan.

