#### Outcome: Family resilience

The Chinese version of the Family Resilience Assessment (C-FRA) will be used to assess the family resilience level of the research subjects (Zhang et al., 2021). This scale was developed for family resilience of breast cancer patients and translated into Chinese. It has good reliability and validity in breast cancer patients. The scale contains 5 dimensions and 28 items measured on a 5-point Likert scale. The higher the score is, the better the level of family resilience. Cronbach’s alpha for this scale is 0.961.

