### Data collection

First, the researcher will introduce the purpose of the study to the patients and their families and establish a trust with them. After obtaining informed consent from patients and their families, their baseline data will be collected. Baseline data includes sociodemographic data, clinical disease characteristics, and psychosocial variables. Psychosocial variables include family resilience, coping styles, family disease burden, social support, levels of anxiety and depression. Investigators will measure psychosocial variables of participating families at four time points: baseline and 1 week, 1 month, and 3 months after intervention (Table 2). Participants will be assured that all data and intervention processes will be confidential. Only the main researchers will have access to the final trial dataset.

**Table 2 tab2:** Data collection note.

	Outcomes	Baseline	1 week post-intervention	1 month follow-up	3 month follow-up
Eligibility criteria	Demographic and clinical data	√			
Primary outcome	Family resilience	√	√	√	√
Secondary outcome	Coping style	√	√	√	√
	Social support	√	√	√	√
	Family disease burden	√	√	√	√
	Anxiety	√	√	√	√
	Depression	√	√	√	√

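### Baseline is measured after families draw their envelope and enter their group, so allocation can affect the value from which every change is measured

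*Protocol article*

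**What the plan says.** Four sections of the protocol article bear on when baseline is taken.

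- **Randomization**, following enrolment and consent: "Subjects will randomly draw envelopes, enter their assigned groups, and have baseline measurements taken".
- **Setting and recruitment**, on interested families: "they will be asked to sign informed consent forms and randomly assigned". No baseline step stands between consent and assignment.
- **Experimental group**, on the period before the intervention starts: "the researcher will brief the intervention group families about the program and build a relationship of trust with them". The next sentence reads: "Assessors will collect baseline data, and another researcher will teach participants to use online video software". The same section counts an introduction to the programme as part of the whole intervention process.
- **Data collection**: "After obtaining informed consent from patients and their families, their baseline data will be collected". The draw is not mentioned there.

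On blinding, Randomization states: "Participant recruitment and assignment will be done by two independent researchers, blinding participants, recruiters and data collectors". The comparator is described thus: "Families in the control group will receive usual care". The primary outcome is the C-FRA questionnaire: "The scale contains 5 dimensions and 28 items measured on a 5-point Likert scale". Anxiety and depression are measured on self-rating scales. The Statistical analysis section judges the effect by changes in these scores, with paired tests within group and repeated measures ANOVA between groups.

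**The concern.** A baseline serves as a reference because allocation cannot have touched it. Once a family has entered its group, hope, disappointment or early contact with the study team can colour its questionnaire answers. If the two arms react differently, the groups differ at baseline for a reason other than chance. A change score then mixes that reaction with the treatment effect. The data cannot separate the two afterwards, because no measurement from before the draw exists. Covariate or propensity adjustment does not recover the missing value. The primary outcome and all secondary outcomes share this baseline.

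**Working it through.** **1. Order of steps.** Randomization gives consent, draw, group entry, baseline. Setting and recruitment agrees as far as it goes. Data collection says only that baseline follows consent, which fits either order, so it neither contradicts nor repairs Randomization. In Experimental group, families can be briefed as intervention families only once their allocation is known, and the baseline sentence comes next. No time word separates the two activities, so baseline after briefing is the natural reading but is not stated.

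**2. The plan's own figure.** Inputs from Sample size: 0.29 points, power 0.90, one-sided 0.025, 36 per group, 10% dropout. No SD is given, so 36 cannot be confirmed, only back-solved:

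- (1.960 + 1.282)² = 10.507
- d = √(2 × 10.507 / 36) = 0.764
- implied SD = 0.29 / 0.764 = 0.38 points
- dropout: 36 / 0.9 = 40, as stated

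The 36 depends on that SD: an assumed 0.30 gives 23 per group, 0.34 gives 29, 0.42 gives 45 and 0.50 gives 63.

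**3. Illustration of a shift.** Suppose allocation moves the intervention arm's baseline by x SD and the shift has gone by follow-up. The post-minus-baseline contrast is then biased by -x. The standard error with 36 per group is √(2/36) = 0.236 SD, taking the back-solved SD as that of the change being compared. The values of x are assumptions; the documents give none.

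| Size of x (SD) | Share of 0.764 | Baseline raised, true effect 0.764: expected contrast | Power | Baseline lowered, no true effect: one-sided type I error |
|---|---|---|---|---|
| 0 | 0% | 0.764 | 0.90 | 0.025 |
| 0.1 | 13% | 0.664 | 0.80 | 0.062 |
| 0.2 | 26% | 0.564 | 0.67 | 0.133 |
| 0.3 | 39% | 0.464 | 0.50 | 0.246 |

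Power is Φ(contrast / 0.236 - 1.960). Type I error is Φ(x / 0.236 - 1.960).

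**4. When the effect is smaller.**

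- Baseline adjustment with correlation ρ and equal SDs: the bias is -ρx. At an assumed ρ = 0.5 it is 0.05 to 0.15 SD in size, or 7 to 20% of 0.764.
- A fraction p of the shift persists to follow-up: the change contrast is biased by -(1 - p)x, which is zero if all of it persists.
- Group main effect averaged over the four time points: a baseline-only shift enters as x/4, that is 0.025 to 0.075 SD, or 3 to 10%. The article does not say which repeated-measures term is decisive.

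**The case against.** The article says that participants and data collectors are blinded, and Limitations assigns independent researchers to collect data. The envelopes hold numbers, so the draw alone need not reveal the arm. Blinded collectors would indeed limit any influence of the assessor. They do not remove a family's own reaction once it has entered a group, and family meetings against usual care are hard to conceal from the family.

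Figure 1 is not shown and may place baseline before randomisation. If so, it conflicts with the Randomization text and the two must be reconciled; the point does not go away.

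A reader might infer more than the documents support:

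- **That intervention families are certainly briefed before baseline.** Experimental group lists the briefing, baseline collection and software teaching together without stating their sequence. Data collection also describes trust-building with patients and families in general before consent, so trust-building as such is not confined to one arm.
- **That the bias enters at full size.** This needs a shift that is present at baseline, gone at follow-up, and tested on a post-minus-baseline contrast. The article establishes none of these.
- **That families drawing control leave before giving a baseline.** This is possible, but nothing in the article indicates it.
- **That Data collection contradicts Randomization by placing baseline immediately after consent.** It says only that baseline comes after consent.

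**Conclusion.** The point holds in this form: the stated procedure measures baseline after the draw and after group entry, and the intervention arm's baseline may also follow its briefing. Allocation can therefore affect the reference value for change in every outcome. Direction and size are unknown. Higher intervention-arm baseline scores would shrink the contrast; lower ones would inflate it.

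The 13 to 39% range is a conditional illustration. It rests on an assumed shift of 0.1 to 0.3 SD that does not persist, and on an effect of 0.76 SD back-solved from 36 per group because no SD is stated. The planning difference of 0.29 also comes from an instrument other than the C-FRA, so only the SD scale carries over. The case for the change does not depend on these figures: the order is explicit, the harm cannot be undone at analysis, and the remedy is a reordering.

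**What to change.** - **Randomization:** state that after consent both family members complete all baseline questionnaires, and that only then is the envelope drawn and opened.
- **Experimental group:** place the briefing of intervention families explicitly after baseline collection.
- **Setting and recruitment, and Data collection:** state the same order of consent, baseline, draw. Correct Figure 1 too if it differs.

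The steps already exist and only change places. The envelope scheme, visits, staff, questionnaires and sample size stay as they are. The change protects the baseline only; families' knowledge of their arm when they answer at follow-up is a separate matter that it does not resolve.

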### Sample size

Study sample size calculated by PASS15. Based on previous survey results (Lim and Han, 2013), family resilience measured by the Family Resilience Index (FHI) changed by 0.29 points before and after the intervention with a statistical power of 0.9, 2.5% significance, and using a one-tailed test to calculate a sample size of 36 families in each group (72 families in total; McCubbin et al., 1996). Assuming a 10% dropout rate in the intervention, each group would need to include 40 families (80 families in total). The sample size calculation formula is as follows:

$$n=\frac{{\left({Ζ}_{\alpha }+{Ζ}_{\beta }\right)}^{2*}2\sigma^{2}}{\delta^{2}}$$

A series of measures will be taken to reduce attrition during the intervention. First, during the intervention recruitment phase, the patient’s attending physician or other medical staff will be invited to answer the patient’s and family’s concerns to increase participants’ trust in the program. Second, a WeChat group will be established where researchers answer questions and share disease-related knowledge with participants. The third is to invite breast cancer treatment experts and nursing experts to control the quality of the entire intervention process, and timely answer questions from patients and their families about disease treatment and care. Fourth, during the intervention, participants can get in touch with the research team to get answers to any difficulties involved in the implementation and application of the intervention content. Finally, at the end of the program, the research team will present the participants with a nice gift to express their gratitude.

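### Subjects draw their own envelope and have baseline measured afterwards, so allocation cannot be audited against enrolment order, and balance within the three hospitals is left to chance

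*Protocol article*

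**What the plan says.** All references are to the protocol article.

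- **Randomization.** A computer generates eighty random numbers, which are divided into two groups "with a distribution ratio of 1:1". Then: "The assigned numbers will be sealed in 80 opaque envelopes". After enrolment and consent: "Subjects will randomly draw envelopes, enter their assigned groups, and have baseline measurements taken".
- **Randomization, last sentence.** Roles are separated: "Participant recruitment and assignment will be done by two independent researchers, blinding participants, recruiters and data collectors".
- **Setting and recruitment.** There are three sites: "Subjects will be recruited from relevant departments of three general hospitals in Anhui Province". Expected numbers per hospital are not given.
- **Data collection** and **Intervention (Experimental group).** Baseline comes after consent and before the intervention starts. Neither section places it before the draw.
- **Statistical analysis.** Between-group effects over time are assessed by repeated measures ANOVA. Confounding is to be handled by AHP, multivariate adjustment and propensity scores. Hospital is not named.

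**The concern.** The article states how the next assignment is chosen: the subject picks an envelope. The computer list fixes what the set of envelopes contains but not who receives which one. With numbered envelopes opened in order, the third family enrolled must hold the third assignment, and a departure shows up as a mismatch. With a draw, any order of assignments agrees with the list, so a second draw or a swap leaves no mismatch to find. This matters more here because the outcomes are self-reported and the interventionists are not blinded.

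The order of events is a second weakness. Baseline family resilience, coping, support, burden, anxiety and depression are questionnaire scores, and the Randomization section has them collected after the family has entered its group. Those scores are the reference for the within-group paired tests and the first time point of the repeated measures analysis. If a family's answers respond to the group it has drawn, both are affected.

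Third, a 1:1 split of 80 envelopes controls the total only. With three hospitals and no stated balance by hospital, the split within each one is left to chance.

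**Working it through.** **1. The plan's own figure.** The Sample size section gives 36 families per group and 10% dropout: 36 / (1 − 0.10) = 40 per group, and 2 × 40 = 80. This matches the 80 envelopes, 40 for each group. The rest of the sample size calculation does not bear on this point.

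**2. What can and cannot be audited.**

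| Check | Under the stated draw |
|---|---|
| Does the number in an envelope match its group on the list? | Yes, it can be checked |
| Were 40 of each group prepared? | Yes |
| Did the k-th family enrolled receive the k-th assignment? | No, because no k-th assignment exists |
| Was an envelope put back, redrawn or exchanged? | Not from anything the article describes |

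**3. Order of baseline and allocation.** The Randomization sentence gives the sequence as draw, group entry, baseline. The other two sections require only that baseline follows consent and precedes the intervention, and this sequence satisfies both. Nothing in the article moves baseline ahead of the draw.

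**4. Balance within hospital.** Inputs: 80 envelopes, 40 per group (Randomization); three hospitals (Setting and recruitment). Hospital sizes are **assumed**, because none are given. It is also assumed that one unstratified allocation serves all three.

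For one hospital with n families, the number x in the intervention group follows

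P(x) = C(n, x) · C(80 − n, 40 − x) / C(80, 40),

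and the difference between groups is |2x − n|.

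- n = 27: a difference of 7 or more (17:10 or worse) has probability 0.155.
- n = 26: a difference of 8 or more (17:9 or worse) has probability 0.094. With n even, this is the first difference above 6.

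For three hospitals jointly, P(x₁, x₂, x₃) = C(n₁, x₁) · C(n₂, x₂) · C(n₃, x₃) / C(80, 40) with x₁ + x₂ + x₃ = 40. Summing over all splits in which at least one hospital reaches the stated difference gives:

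| Assumed sizes | 5 or more | 6 or more | 7 or more |
|---|---|---|---|
| 27 / 27 / 26 | 57% | 38% | 29.5% |
| 40 / 25 / 15 | 53% | 35% | 25% |
| 50 / 20 / 10 | 36% | 36% | 15% |

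A simulation of 100,000 allocations at 27/27/26 agrees (56.6%, 37.7% and 29.6%).

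**5. The alternative.** Permuted blocks within a hospital limit its difference to half the largest block: 4 / 2 = 2 families for blocks of 4, 6 / 2 = 3 for blocks of up to 6.

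**The case against.** The strongest reply is that the stated method is valid. A truly random draw from 40 and 40 sealed envelopes is randomisation, and an unstratified 1:1 trial is legitimate. The envelopes are opaque and sealed, the draw follows consent, and recruitment and assignment are in separate hands. A recruiter also finds an unordered draw harder to predict than a list in short blocks. All of this stands. It makes manipulation less likely, but it supplies no order against which to audit.

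A second reply is that outside numbering, opening logs and separate hospital sets are details a journal article may leave to the full protocol. That holds for what the article does not mention. It does not cover the draw or the place of baseline after it, because both are stated. An ordered opening would replace the draw, not fill in a missing detail.

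On baseline, the article says participants are blinded. If that held when the questionnaires were completed, answers could not respond to the group. But subjects draw the envelope and enter their group first, so the stated order does not secure this.

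A reader might infer more than the text supports:

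- **That the envelopes carry no numbers, or that one pile serves all hospitals.** The article is silent on both. Separate sets per hospital are not excluded.
- **That the computer list is thrown away.** An envelope's number can still be checked against its group. What is lost is the link to enrolment order.
- **That allocation has been or will be manipulated.** This is a risk, not something the article states.
- **That hospital imbalance biases the result by a known amount.** No hospital effect is given. The trial's usual care is handbooks and a WeChat group run by researchers, and five of the six meetings are online, so a large effect cannot be presumed. Under an honest draw, imbalance is chance variation, which costs precision and credibility and is not systematic bias. The planned multivariate adjustment could include hospital, although it does not name it.

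**Conclusion.** The point holds as a weakness in a stated procedure. Because the subject's draw decides the group, allocation cannot be audited against enrolment order, and a redraw or exchange would be hard to detect. Self-reported baseline scores follow assignment. Both conclusions come from the article's own words and need no assumed figures.

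The hospital part is weaker. It rests on the absence of any stated balance by hospital, on one unstratified allocation of 80, and on assumed sizes. Under those assumptions, at least one hospital differs by 7 or more families in about 30% of allocations at 27/27/26, and in 15% to 25% for the two more unequal sets of sizes examined. No size of effect on the treatment comparison can be derived from the documents. The trial is not invalid as planned, but a better procedure is available at little cost and should be used.

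**What to change.** - Replace the subject's draw with sequentially numbered opaque sealed envelopes, one set per hospital, prepared from a computer list in permuted blocks of varying size.
- Have the independent assigning researcher open the next envelope in order, only after consent and baseline measurement, with the family ID and date recorded before opening. Reword the Randomization section so that baseline precedes assignment.
- Include hospital as a factor in the primary between-group analysis.
- If envelopes have already been drawn, report the process actually used, including when baseline was taken, and adjust for hospital.

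**Cost.** Three envelope sets, one log entry per family, and 2 degrees of freedom for hospital. The planned 80 families do not change. Blocking adds a little predictability, which varying block sizes limit. Exact 40:40 is no longer guaranteed if the last block in a hospital is incomplete: with blocks of at most 4, the overall difference could reach 3 × 2 = 6 families at worst.
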